**Figure figure2:**
[figure not shown]
Screenshot of the homepage of the patient interface of Grip self-help.

^c^MUS: medically unexplained symptoms.

^d^Not applicable.

^e^DIBQ: Determinants of Implementation Behavior Questionnaire.

^f^SCQ-3: Social Communication Questionnaire–3.

All instruments are self-report questionnaires. Participants will receive automated emails containing a link to the questionnaires. If participants have not filled out the questionnaires, automated email reminders will be sent after 1 and 2 weeks. If participants have not filled out the questionnaires after these reminders, a research assistant will call to remind them.

If participants decide to withdraw from the study before they have completed the study protocol, the main reason for withdrawal will be inquired. Also, participants will be asked to complete the Web-based questionnaires at follow-up after 16, 26, and 52 weeks.

### Instruments

#### Health-Related Quality of Life

We will use the validated Dutch version of the 36-item General Health Survey (RAND-36) to assess HRQoL. The RAND-36, which is nearly identical to the SF-36, is a self-report questionnaire for measuring general health status [15,16]. In this study, the 8 subscales will be aggregated into 2 summary scores: the physical and mental component score. The physical component score comprises 4 subscales: general health, bodily pain, physical functioning, and role limitations because of physical problems. The mental component score also comprises 4 subscales: vitality, mental health, social functioning, and role limitations because of emotional problems. Scores range between 0 and 100, with a higher score representing a better HRQoL*.*

#### Symptom Severity

Severity of MUS will be assessed with the Somatization subscale of the 4-Dimensional Symptom Questionnaire (4DSQ). The 4DSQ is a validated 50-item Dutch self-report questionnaire, developed and widely used in general practice to assess somatization, distress, anxiety, and depression [14]. The somatization subscale considers the frequency of 16 common physical symptoms over the past week with a score range between 0 and 32.

The 4DSQ will also be used to assess distress (subscale with 16 items, score range 0-32) and symptoms of anxiety (subscale with 12 items, score range 0-24) and depression (subscale with 6 items, score range 0-12). Higher scores refer to more symptoms.

#### Costs

The Medical Consumption Questionnaire (*i*MCQ) will be used to measure health care utilization. The *i*MCQ is a 31-item Dutch self-report questionnaire aimed to assess the direct costs of health care [17]. These are the costs of treatment, care and rehabilitation related to illness or injury and include expenditures for physicians and other health care professionals, care in hospitals and other institutions, and medication. We added extra items to the *i*MCQ to measure costs associated with contacts with a GP-MHW.

The Productivity Costs Questionnaire (*i*PCQ) will be used to assess productivity loss. The *i*PCQ is a 12-item Dutch self-report questionnaire aimed to measure indirect costs related to illness or injury [18]. These are the costs of productivity loss as a result of absence from work or inefficiency during paid or unpaid work.

#### Patient Acceptability

A Dutch translation of the Client Satisfaction Questionnaire-8 (CSQ-8) will be used to assess patient satisfaction with the study intervention [19]. The internal consistency of this scale in the Dutch population is very high. The 8-item self-report questionnaire has a score range from 8 to 32.

### Other Variables

Demographic information (eg, age, sex, educational level, and marital status), internet experience, and type and severity of main presenting symptom will be assessed at baseline. As a mediator, self-efficacy will be assessed by the Self-Efficacy Scale [20].

In addition, the GP and GP**-**MHW will be asked to fill out a number of questionnaires. The PCP’s attitude toward MUS will be assessed using a 24-item questionnaire. Potential determinants for health care professional implementation behavior will be examined using a selection of 13 items from the Determinants of Implementation Behavior Questionnaire [21]. The PCP’s attitudes with regard to risks and benefits of electronic health (eHealth) and their own computer skills will be assessed with the Dutch 18-item eHealth Attitude Questionnaire [22]. To assess PCP acceptability of Grip self-help, PCPs in the intervention group will complete the core item set of the CSQ-8, adjusted for use by health care professionals (CSQ-3).

#### Sample Size

Our power analysis is based on the effect estimates, calculated in our previous meta-analysis on the effectiveness of self-help interventions for MUS [11]. For HRQoL, we observed an effect size (Hedges g) of 0.66. As there was some evidence of publication bias toward larger effect sizes and because this meta-analysis also included studies with a waiting list control group, we based our calculations on an effect size of 0.5 (moderate effect). Without correcting for clustering by practice, the sample size based on an unpaired *t* test, given an effect size of 0.5, adopting power (1−beta) of .8, and alpha .05 2-sided, is 128. Accounting for 20% dropout, the number of patients that needs to be included is 1.25×128=160. On the basis of previous Dutch studies on MUS in general practice, we expect that a GP can include 4 patients during the inclusion period. To adjust the sample size for clustering by GP we calculated the design factor as: 1+(cluster size−1)×intraclass correlation coefficient (ICC). ICCs of 0.01 are recommended for the primary care setting [23], and the design factor then is 1+(4−1)×0.01=1.03. Consequently, a total of 1.03×160=165 patients need to be included, with an estimated number of 41 GPs.

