### Participants

Patients with mild to moderate MUS will be recruited through general practices from rural as well as urban areas in the Netherlands. Of the PCPs, 2 types will be involved in this study: GPs and general practice mental health workers (GP-MHWs). GP-MHWs are nurses, psychologists, or social workers with experience in mental health care, employed by one or several general practices. PCPs will be invited to participate through local and national GP networks, social media, and Web publicity. PCPs that show interest will be informed by a letter. If desired, more detailed information can be provided by email, telephone, or during a visit to the practice. At least 1 GP and 1 GP-MHW are required to participate for a practice to take part in the study. Participating PCPs sign an informed consent form. Subsequently, the GP selects up to 15 patients with mild to moderate MUS based on the inclusion criteria described in Textbox 1. Selected patients receive a letter with information about the study. During a telephone call with one of the researchers, additional questions from interested patients will be answered and exclusion criteria (see Textbox 1) will be evaluated. When eligible patients decide to participate in the study, they will be asked to sign an informed consent form. Next, the participant will receive an email with an invitation to fill out the baseline questionnaires in a Web-based secure environment. An overview of the study procedure is provided in Figure 1.

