### Randomization Procedure

Randomization will be performed at general practice level. After all participants from a practice have given informed consent and filled out baseline questionnaires, practices will be randomly assigned to the intervention (Grip self-help) or control (CAU) group, using Web-based randomization tool ALEA (ALEA Clinical | FormsVision). Randomization after patient inclusion prevents the possibility of recruitment bias (selection bias). Randomizing general practices rather than patients will avoid PCPs within a practice offering both Grip self-help and CAU, as this could cause contamination effects. Randomization will take place in blocks, randomly varying in size between 4 and 8, and a 1:1 allocation ratio.

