### Statistical Analyses

Primary analysis will be performed on an intention-to-treat basis, meaning that all subjects that were allocated to either the intervention or the control group are included in the analysis and analyzed in the groups to which they were randomized. Secondary analyses will be performed on a per-protocol basis. The Grip self-help intervention is considered per-protocol if the last exercise has been completed. If, despite randomization, important baseline differences exist in prognostically important variables, they will be adjusted for by including them as covariates.

Differences in the effectiveness of Grip self-help compared with CAU will be analyzed using linear mixed-models (LMM), with HRQoL (RAND-36) and symptom severity (4DSQ) as outcomes. LMM allow correcting for dependence of (repeated) observations within patients as well as possible variations between practices. LMM have shown to be superior for the analysis of longitudinally correlated data and can optimally deal with missing values (no imputation needed) and cluster effects [24].

For the remaining analyses, missing values will be imputed using multiple imputation (MI). Both LMM with incomplete data and MI require the assumption of data being missing at random. Although this assumption is not testable, we will study the missing data mechanism by studying predictors of *missingness* of data using multivariable logistic regression analyses. The final imputation model will comprise all variables used in the analyses and all variables that predict *missingness* of a certain variable or its value.

The cost-effectiveness of Grip self-help compared with CAU will be investigated from a societal perspective, which includes costs in- and outside the health care sector (*i*MCQ and *i*PCQ). Results will be expressed in terms of incremental costs per quality-adjusted life year gained.

Acceptability of the Grip self-help intervention for patients and PCPs will be assessed using CSQ-8 and CSQ-3 scores.

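### The design factor treats the GP as the cluster although practices are randomised, so 165 patients at 80% power fit the design only if each practice contributes about one GP, which is not stated

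*Protocol article*

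**What the plan says.** Protocol article, Randomization Procedure: "Randomization will be performed at general practice level". A practice is allocated only once all its participants have consented and completed baseline.

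Participants: "At least 1 GP and 1 GP-MHW are required to participate for a practice to take part in the study". This sets a minimum of one GP. Neither a maximum nor an expected number of GPs per practice is given.

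Sample Size: the paragraph begins at practice level, giving the unadjusted size "Without correcting for clustering by practice". It then changes unit: "we expect that a GP can include 4 patients during the inclusion period", and "To adjust the sample size for clustering by GP we calculated the design factor". The ICC is justified by "ICCs of 0.01 are recommended for the primary care setting". The result is 165 patients, "with an estimated number of 41 GPs". No number of practices is given.

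Statistical Analyses: the linear mixed model is said to correct for repeated observations within patients and for "possible variations between practices".

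**The concern.** In a cluster-randomised trial, power depends on the number of randomised units and on how many patients each unit holds. Here the unit is the practice in the randomisation and in the analysis model, but the GP in the design factor. If practices enter more than one GP, the cluster is a multiple of 4 patients and the number of randomised units is well below 41.

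Two things follow. The inflation of 1.03 would be too small. The trial could also reach 165 patients and 41 GPs with far fewer practices than a reader would suppose, while the stated power stayed at 80%. The article says enrolment was still under way, so an explicit practice target could still have guided recruitment.

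**Working it through.** **Inputs from the Sample Size section:** standardised effect 0.5; two-sided alpha 0.05; power 0.80; dropout 20%; 4 patients per GP; ICC 0.01. **Assumed, because the article gives no figure:** 2 or 3 participating GPs per practice.

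**Step 1. Reproduce the plan's figure.**
- Unpaired t test: 63.77, rounded up to 64 per arm, so 128.
- Dropout: 128 / (1 − 0.20) = 160.
- Design factor: 1 + (4 − 1) × 0.01 = 1.03.
- Total: 1.03 × 160 = 164.8, so 165.
- GPs: 165 / 4 = 41.25, about 41.

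Every figure reproduces.

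**Step 2. Same formula with the practice as cluster.** Let m be the patients per practice (GPs per practice × 4). The factor is 1 + (m − 1) × 0.01 and the required total is 160 × factor.

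| GPs per practice | m | Practices for 165 patients | Factor | Required total |
|---|---|---|---|---|
| 1 | 4 | 165/4 ≈ 41 | 1.03 | 164.8 → 165 |
| 2 (assumed) | 8 | 165/8 ≈ 21 | 1.07 | 171.2 → 172 |
| 3 (assumed) | 12 | 165/12 ≈ 14 | 1.11 | 177.6 → 178 |

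**Step 3. Power that 165 patients give.** With 20% dropout, 165 × 0.8 = 132 are analysed. Power is the two-sided t-test power with noncentrality 0.5 × √(132 / (4 × factor)). Two choices are shown for cluster size: as enrolled (m), and as analysed (0.8 × m), which is the more lenient.

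With patient-level degrees of freedom, as in the plan's t test:

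| GPs per practice | Enrolled m | Analysed 0.8 × m |
|---|---|---|
| 1 | 80.2% | 80.5% |
| 2 | 78.7% | 79.3% |
| 3 | 77.2% | 78.1% |

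With practice-level degrees of freedom (number of practices − 2) and analysed cluster sizes:
- 1 GP: about 79%.
- 2 GPs: 75–76%. The factor is 1 + (6.4 − 1) × 0.01 = 1.054 and the noncentrality 2.80, on about 19 degrees of freedom.
- 3 GPs: 71–72%. The factor is 1.086 and the noncentrality 2.76, on about 12 degrees of freedom.

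**Step 4. Separate the two effects.** Changing the cluster unit alone costs 80.2 − 78.7 = 1.5 points for 2 GPs and 80.2 − 77.2 = 3.0 points for 3 GPs (enrolled m). The rest of the fall comes from having fewer randomised units. That part already takes about a point at one GP per practice.

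**The case against.** The strongest reply is that the paragraph may simply treat one GP as one practice. It passes from practice to GP without comment, the minimum is one GP, and the recruitment text speaks of the GP in the singular. On that reading 165 and 80% stand. There is also some slack: with analysed cluster sizes and patient-level degrees of freedom, power is 80.2% at 5 patients per practice and 79.9% at 6. A t test with a design factor is a common planning approximation, and the degrees-of-freedom method of the mixed model may properly sit in an analysis plan not shown here.

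Much of this stands. No passage shows that practices typically enter several GPs, and the effect of the unit alone is small at an ICC of 0.01. What remains is that the one-GP reading is stated nowhere, the eligibility rule allows more, and the section gives no number of randomised units.

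A reader might infer more than the document supports:
- *That 165 is an arithmetic error.* It is not; the issue is the input. Nor do 41 GPs need correcting: 165 / 4 = 41.25, and the number is described as estimated.
- *That the power holds only with exactly 4 patients in every practice.* The factor uses an average, and the slack above shows otherwise.
- *That clusters could hold 15 patients per GP.* That figure is the number a GP may select for an invitation letter, before interest, screening and consent. It is not an enrolled cluster size.
- *That the loss is severe because the true ICC is higher.* A higher ICC would enlarge it, but the plan's cited value is 0.01 and the document offers no other.
- *That adjusting for the baseline score makes up the loss.* This depends on the correlation between baseline and follow-up, which the document does not give.

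**Conclusion.** The point holds in a conditional form. The design factor is computed at GP level, while randomisation and the described model are at practice level. The stated 165 patients and 80% power match the design if a practice contributes about one GP, and otherwise somewhat overstate the power.

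At the plan's ICC of 0.01, an average of 2 to 3 GPs per practice (assumed) means 7 to 13 more patients for the same power (172 − 165 and 178 − 165). With 165 patients, power is about 77–79% on patient-level degrees of freedom and about 71–76% on practice-level ones. The document does not support the unconditional reading that the trial is underpowered. It supports saying that the number of randomised practices, on which the power depends, is left open by a calculation done at another level. This should be corrected, but it does not undermine the design.

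**What to change.** Rewrite the sample-size paragraph with the practice as cluster throughout:
1. Give the expected number of participants per practice (expected GPs per practice × 4) and recompute the design factor from it.
2. State the expected number of practices to be randomised, not only the number of GPs.
3. Restate the power that 165 patients give at that level, and say whether practice-level degrees of freedom were used.

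Alternatively, if each practice is meant to contribute one GP, say so as a design assumption. The existing 1.03 and 165 then stand, and 41 becomes the expected number of practices.

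The cost is one revised paragraph and, if several GPs per practice are expected, a slightly less favourable stated power.

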### Statistical Analyses

Primary analysis will be performed on an intention-to-treat basis, meaning that all subjects that were allocated to either the intervention or the control group are included in the analysis and analyzed in the groups to which they were randomized. Secondary analyses will be performed on a per-protocol basis. The Grip self-help intervention is considered per-protocol if the last exercise has been completed. If, despite randomization, important baseline differences exist in prognostically important variables, they will be adjusted for by including them as covariates.

Differences in the effectiveness of Grip self-help compared with CAU will be analyzed using linear mixed-models (LMM), with HRQoL (RAND-36) and symptom severity (4DSQ) as outcomes. LMM allow correcting for dependence of (repeated) observations within patients as well as possible variations between practices. LMM have shown to be superior for the analysis of longitudinally correlated data and can optimally deal with missing values (no imputation needed) and cluster effects [24].

For the remaining analyses, missing values will be imputed using multiple imputation (MI). Both LMM with incomplete data and MI require the assumption of data being missing at random. Although this assumption is not testable, we will study the missing data mechanism by studying predictors of *missingness* of data using multivariable logistic regression analyses. The final imputation model will comprise all variables used in the analyses and all variables that predict *missingness* of a certain variable or its value.

The cost-effectiveness of Grip self-help compared with CAU will be investigated from a societal perspective, which includes costs in- and outside the health care sector (*i*MCQ and *i*PCQ). Results will be expressed in terms of incremental costs per quality-adjusted life year gained.

Acceptability of the Grip self-help intervention for patients and PCPs will be assessed using CSQ-8 and CSQ-3 scores.

To investigate which patient characteristics predict effectiveness of Grip self-help, Least Absolute Shrinkage and Selection Operator linear regression will be performed in the intervention group. Interaction terms of demographic variables and problem profile scores x treatment group will be entered as predictors, the physical component score of the RAND-36 at the end of treatment will be the outcome. For these analyses, the MI procedure will be performed separately in the treatment groups to allow for different associations between predictor and outcome in the Grip self-help and control condition.

To investigate which characteristics of PCPs predict effectiveness of Grip self-help, analyses of subgroups of these characteristics (eg, attitude toward MUS, eHealth attitude, and determinants for implementation behavior) will be performed, followed by statistical significance testing of the pertaining subgroup indicator xGrip self-help interaction term. As our sample calculation did not reckon with subgroup analyses, we consider these analyses exploratory in nature.

To investigate whether increased self-efficacy mediates treatment outcomes, we will use the regression-based method proposed by Preacher and Hayes [25].

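### Primary care professional (PCP) scale scores are to be tested as subgroup indicators; with about 41 GPs, a continuous score × treatment term would use the same data better

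*Protocol article*

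**What the plan says.** Secondary objective 5 (Objective) asks which PCP characteristics predict the effectiveness of Grip self-help. Under Statistical Analyses the article states the method in two steps. First, "analyses of subgroups of these characteristics (eg, attitude toward MUS, eHealth attitude, and determinants for implementation behavior) will be performed". The second step, which supplies the formal test for each characteristic, is "statistical significance testing of the pertaining subgroup indicator xGrip self-help interaction term". On the status of this work the authors add: "As our sample calculation did not reckon with subgroup analyses, we consider these analyses exploratory in nature".

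Other Variables describes how the named characteristics are measured:

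- MUS attitude: "The PCP’s attitude toward MUS will be assessed using a 24-item questionnaire".
- Implementation determinants: "a selection of 13 items from the Determinants of Implementation Behavior Questionnaire".
- eHealth attitude and computer skills: these "will be assessed with the Dutch 18-item eHealth Attitude Questionnaire".

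Table 2 places all three at baseline. Sample Size expects 165 patients from an estimated 41 GPs, with 4 patients per GP, an ICC of 0.01 and 20% dropout. Randomization is by practice, 1:1.

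**The concern.** The characteristics named as examples come from multi-item questionnaires, which normally give graded scores. The plan nevertheless tests membership of a subgroup. Turning a graded score into an indicator treats all professionals on one side of a cut as alike and discards the differences among them.

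This matters more here than for a patient-level characteristic, because the moderator varies between professionals and not between patients within a practice. About 41 GPs is roughly 20 per arm, or about 10 per cell once each arm is split in two. A real modifier becomes harder to detect, and a null result says less. Only secondary objective 5 is at stake.

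The same section enters patients' problem profile scores in interaction terms with treatment and does not mention grouping them. Score-based interactions are therefore already part of this plan.

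**Working it through.** **1. The plan's own figures.** An unpaired t test with effect size 0.5, two-sided alpha 0.05 and power 0.80 needs 63.77, so 64 per arm, 128 in all. With dropout: 1.25 × 128 = 160. Design factor: 1 + (4 − 1) × 0.01 = 1.03. Then 1.03 × 160 = 164.8, so 165 patients, and 165/4 = 41.25, so about 41 GPs. All of these reproduce. The article gives no figure for the PCP analysis.

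**2. Information kept by grouping.** Assume that the treatment effect changes linearly with the score. The share of information kept is then the squared correlation between the score and its grouped version. For a normal score cut in two at proportion p, with z_p the normal quantile and φ the normal density, it is φ(z_p)² / [p(1 − p)].

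| Score and grouping | Kept | Lost |
|---|---|---|
| Normal, median split | 2/π = 63.7% | 36.3% |
| Normal, 30/70 | 57.6% | 42.4% |
| Normal, 20/80 | 49.0% | 51.0% |
| Normal, tertiles | 79.3% | 20.7% |
| Normal, quartiles | about 86% | about 14% |
| Uniform, median split | 75.0% | 25.0% |

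For a normal score, the median is the best place for a single cut, so 36.3% is the smallest two-group loss. In GP terms, 41 × 0.637 = 26: a median split works as if about 26 of the 41 GPs had been used.

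**3. Effect on power, large-sample formula.** If the continuous term has 80% power, power after grouping is Φ(√kept × (1.960 + 0.842) − 1.960).

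- Normal score, median split: 0.798 × 2.802 − 1.960 = 0.276, so Φ = 60.8%.
- Uniform score, median split: 0.866 × 2.802 − 1.960 = 0.467, so Φ = 68.0%.

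**4. Simulation at the planned size.** There are 41 GPs (21 and 20 per arm). Each has 3 analysed patients, because 4 × 0.8 = 3.2. The ICC is 0.01, so the variance of a GP mean is 0.01 + 0.99/3 = 0.34. The score is normal, the average effect is 0.5 SD, and the interaction is tested in a regression of GP means at two-sided 0.05. There were 15,000 runs per row. The interaction sizes are assumptions.

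| Interaction (SD per SD of score) | Continuous | Median split |
|---|---|---|
| 0.1 | 8% | 7% |
| 0.2 | 18% | 13% |
| 0.3 | 33% | 22% |
| 0.4 | 53% | 35% |
| 0.56 | 79% | 57% |

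Repeat runs with fewer replicates gave 52% against 34–36% at 0.4.

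**The case against.** The best defence is that the authors already limit what they claim. They say that the sample size did not allow for these analyses and call them exploratory. They also plan a formal interaction test and do not compare p-values within subgroups. The planned test is valid, and nothing is miscalculated. All of this stands and keeps the severity low. It does not favour the indicator, however: low power is a reason to use the whole score.

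A second defence is that the gain is modest where modifiers are weak. This also stands. At 0.1 or 0.2 SD per SD both tests have little power. An interaction of 0.4 is strong: with an average effect of 0.5 SD it means effects of 0.1 and 0.9 SD at one SD below and above the mean score. The number of GPs remains the main limit under either method.

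Three stronger readings are tempting, and the article does not support them:

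- A reader might infer that at least a third of the information is always lost. The article fixes neither the number of groups nor the distribution of the scores, and the table shows smaller losses. If the true effect were a step at the cut, a split there would not incur this loss.
- A reader might infer from the absence of cut-points that they will be chosen after seeing the data. A condensed article may leave such definitions to the full protocol or SAP, so their absence is no finding.
- A reader might infer that every PCP characteristic is a continuous score. The list is given only as examples, and the article does not say how the 13 selected items or the 24-item questionnaire are scored. For categorical characteristics, such as professional background, an indicator is the natural form.

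**Conclusion.** The point holds as a matter of efficiency. The article names the indicator × treatment interaction as its test, so this is a stated choice and not an omission. Where a questionnaire yields a scale score, a continuous term addresses the same question from the same data with more power.

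The size is conditional. The loss is about 36% or more for a two-group split of a roughly normal score with a linear effect, and about 20–25% for tertiles of a normal score or a median split of a uniform one. At an assumed interaction of 0.4 SD per SD, power is about 52% against about 35%. The figure of 41 GPs is itself approximate: practices are the randomized unit and may be fewer, and the practice mental health workers also complete questionnaires.

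The severity is low. The primary analysis, its error rate and the sample size do not depend on this choice.

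**What to change.** Replace the sentence on PCP characteristics with wording to this effect: for each PCP characteristic that yields a scale score, the standardised score, treatment and their interaction will be entered in the linear mixed model with a random effect for practice, and the interaction term will be tested. Linearity will be checked with a plot or a quadratic term. Estimated treatment effects will be shown at, for example, −1, 0 and +1 SD of the score, and subgroups will be used for display only. Characteristics that are truly categorical will keep an indicator × treatment term. All these analyses remain exploratory.

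The cost is a sentence or two of analysis wording, with no extra data and no change to conduct. The one new assumption is linearity, which the plot or quadratic term examines.
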